## Appendix:

The unforeseen global Covid-19 pandemic resulted in that almost all elective benign surgery in Scandinavia was cancelled from March 2020. Thus, the pandemic had severe consequences on the recruitment to the BEST trial during 2020-2021.

During autumn of 2021 the BEST steering committee decided to perform an additional analysis of the power for primary endpoints.

Additional information (Courcoulas et al, JAMA Surg 2020 March; Howard et al, JAMA Surg 2021 Dec) revealed that the risk of any of the predefined substantial adverse events after bariatric surgery is higher than previously anticipated in the revised power calculation, i.e. >25% instead of 13%. These figures were confirmed in an analysis of real-world data from the bariatric national quality register SOReg in Sweden which registered all patients undergoing sleeve or bypass in Sweden since 2007.

An independent statistician performed the analysis based on information above, but also on 2-year data in BEST. In conclusion, it was stated:

Two post hoc power analyses were conducted based on the data from February 2022:

*1. Weight reduction. In the protocol the following is stated "This sample size will also have >95% power to evaluate non-inferiority of 5% weight loss difference over 5 years between the two groups, assuming 15 kg standard deviation in weight loss over follow-up with two-sided 2.5% significance level.". The post hoc power calculation is based on the two-year follow up data where an average weight loss for all patients (both groups, N=1031) of 29.3 kg was attained with a Sd=21.6. Given a loss to follow up of 20% from 2 year follow up to the 5-year follow up the sample size is assumed to be  $(1031 \cdot 0.80)/2 = 413$  patients per group. With a non-inferiority level of 5 kg weight loss the power is found to be 90% if  $n=393$  per group, and 95% if  $n=486$  per group (<https://www.sealedenvelope.com/power/continuous-noninferior/>).*

*2. Substantial adverse events. This post hoc power calculation is for a superiority test where the rate is assumed to be 25% for the gastric bypass at 5 years and sleeve would have a 35% lower level, i.e.  $25\% \cdot 0.65 = 16.25\%$ . Given a sample of  $n=413$  per group the post hoc power will then be 87.5%.*

Taking information above into account and in the interest of not prolonging inclusion period unnecessarily the trial steering committee took a decision to stop inclusion in BEST during spring 2022 (final date 31st of March). At termination of inclusion the number of participants that had been included and operated in BEST were 1752. The trial DSMC reviewed and supported the decision before termination of recruitment to the BEST trial.

1

2

3 Statistical analysis plan for:

4

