## 2. Study objectives

The objective of the study is to evaluate the safety and effectiveness of SG compared to GBP in obese patients eligible for bariatric surgery.

The study has two primary objectives, evaluating superiority and non-inferiority. The study hypothesis for superiority is that patients treated with SG will experience fewer adverse events during the 5-year follow-up as compared to patients treated with GBP.

For non-inferiority, the study hypothesis is that the weight loss in the SG group, as compared to GBP, is within a non-inferiority margin of 5% at 5 years after surgery.

Secondary objectives of the study include health economics, inpatient hospital and outpatient care, drug consumption, alcohol abuse, fractures and bone quality, diabetes, cancer, mortality, and quality of life.

Predefined subgroup analyses will be done by sex, age, diabetes status and body mass index (BMI).

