## 4. Study outcomes

A list of substantial adverse events in bariatric surgery (tabl 2) was predefined before study start. Possible occurrence of any of these will be identified in the CRF (SOREg) but additionally from the national quality health care registries (listed above) during 5-years of follow-up. A superiority of SG over GBP would require >35% fewer patients experiencing one or more substantial adverse event.

Time to occurrence of first substantial adverse event will be analysed as the co-primary outcome. Patients will be defined as either having or not having an event, and thus the number of events in the same patients will not be summarized.

For non-inferiority, weight loss difference over 5-years in patients operated with SG as compared to GBP will be evaluated with regards to the non-inferiority margin of 5%.

Table 1: Primary outcomes:

| Outcome                    | Time frame                  | Explanation                                                                          |
|----------------------------|-----------------------------|--------------------------------------------------------------------------------------|
| Weight loss                | At 5 years after surgery    | Change in weight from baseline in % of total body weight                             |
| Substantial adverse events | Over 5 years after surgery. | Number of patients with any substantial adverse events defined according to table 2. |

Table 2: Substantial adverse events: (events that may have a significant and/or longstanding effect on patients' health and/or everyday life).

| Substantial adverse event              |                                                                                                                                                                                                                                                                                               |
|----------------------------------------|-----------------------------------------------------------------------------------------------------------------------------------------------------------------------------------------------------------------------------------------------------------------------------------------------|

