### 5.1 Sample size and power

153

154 The sample size calculation is based on evaluation of the primary objectives. For evaluation of  
 155 superiority, it is assumed that 13% of patients who undergo GBP will have substantial adverse events  
 156 (as defined in the Study outcomes) over 5 years. It is further assumed that this risk is 35% lower in  
 157 patients in the SG group. Based on these assumptions, it is estimated that a total of 2100 patients  
 158 (1050 in each group) will be required to detect a difference in time to substantial adverse event with  
 159 >90% power at two-sided 2.5% significance level using Cox proportional hazards regression model.

160 Initially the power calculation was based on a SAE rate of 5% over 5 years, leading to the need to  
 161 include 4000 patients (especially regarding subgroup analysis). Partly due to slower than expected  
 162 inclusion rate, but mainly based on data suggesting more events of substantial adverse events than  
 163 expected (i.e., 13%) the sample size was recalculated to n=2100 to obtain sufficient power.

164 This sample size will also have 90% power to evaluate non-inferiority of 5 % weight loss difference  
 165 over 5 years between the two groups, assuming 15 kg standard deviation in weight loss over follow-  
 166 up with two-sided 2.5% significance level.

167

168 See appendix for an updated, post hoc, power-calculation before the closure of the trial inclusion.

169

170 

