### 5.3 Statistical analyses

Summary tables (descriptive statistics and frequency tables) will be provided for all baseline variables, outcome variables, and safety variables, as appropriate. Continuous variables will be summarized with descriptive statistics (n, mean, standard deviation, range, and median). Frequency counts and percentage of subjects within each category will be provided for categorical data.

Incidence of substantial adverse events will be analysed with time-to-event models. Time to first substantial adverse event (as defined in chapter 4 Study outcomes) from primary surgery will be recorded. Kaplan-Meier estimates of cumulative incidence of adverse events will be calculated in both treatment groups. Treatment effect will be calculated as a hazard ratio, together with corresponding confidence interval and p-value for the test of equal hazard ratio, from Cox proportional hazard regression model. The proportionality assumption of the Cox models will be evaluated graphically using "log-log" plots.

The primary conclusions will be based on a model which includes study centre as a covariate together with indicator for treatment. Explorative analyses will be conducted using sex, age, body mass index, smoking and diabetes at baseline as covariates.

For non-inferiority, the difference in weight loss between treatment groups and its confidence interval will be calculated and evaluated against the non-inferiority margin of 5%. The weight loss difference at 5-year follow-up will be estimated with a multilevel mixed-effect regression models utilizing body weight measurements at all available time points. This model takes into account the repeated measurements nested within persons over time. All randomized patients except those who have withdrawn their consent will be included in this analysis, independent of availability of body weight data during the follow-up. The primary conclusions will be based on a model which includes study center in addition to indicator for treatment.

For secondary outcomes, incidence of comorbidities during the follow-up will be evaluated with time-to-event models, and for continuous variables mixed-effect regression models will be used to evaluate differences between the treatment groups.

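### The weight non-inferiority margin is 5% in the SAP's decision rule but 5 kg in the appendix power calculation, and the scale of the modelled difference is not stated

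*Combined protocol and SAP*

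**What the plan says.** The parts of SAP version 5 that set the rule all use a percentage. Section 2 (Study objectives) says the SG result "is within a non-inferiority margin of 5% at 5 years after surgery". Section 4 repeats 5%, and its Table 1 defines the outcome as "Change in weight from baseline in % of total body weight". Section 5.3 has the difference "evaluated against the non-inferiority margin of 5" percent. None of the margin sentences says what the 5% is a percentage of; that has to be taken from Table 1.

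The power statements use kilograms. Section 5.1 reads "This sample size will also have 90% power to evaluate non-inferiority of 5 % weight loss difference", and the same sentence continues "assuming 15 kg standard deviation in weight loss". Appendix item 1 first repeats the 5% wording from the protocol (there with power above 95%). It then takes 2-year data, "average weight loss for all patients (both groups, N=1031) of 29.3 kg was attained with a Sd=21.6", allows for attrition ("Given a loss to follow up of 20% from 2 year follow up to the 5-year follow up") to reach 413 per group, and concludes "With a non-inferiority level of 5 kg weight loss the power is found to be 90" percent at 393 per group and 95% at 486.

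Section 5.3 estimates the 5-year difference from a mixed model using all body weight measurements. It does not say whether the modelled response is weight in kg or percent change from baseline. The protocol's section on the primary outcome gives no numerical margin.

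**The concern.** The margin decides one of the two primary conclusions, so its unit and base should be fixed before the 5-year data are analysed. As written, a model in kg could be compared with a margin in percent, and the only worked calculation in the SAP uses 5 kg.

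An example shows what is at stake. Suppose the mean baseline weight is 120 kg (an assumption; the documents give none) and the unfavourable confidence limit is a deficit of 5.5 kg for SG. Against 5 kg, SG fails. Against 5% of body weight, 5.5/120 = 4.6%, and SG passes.

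The stated power figures are affected too. They are on a different scale from the outcome they are meant to support, and the appendix figures formed part of the grounds for closing inclusion at 1752 rather than 2100 patients.

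**Working it through.** **Inputs.** Appendix: margin 5 kg, SD 21.6 (kg by context), 413 per group (1031 × 0.80 / 2 = 412.4). Section 5.1: SD 15 kg, 1050 per group, stated power 90%. Section 5.2: two-sided 2.5% for primary outcomes, which for non-inferiority is one-sided 1.25%. A true difference of zero is assumed throughout, and no attrition beyond the sample sizes shown.

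**Formulas.** n per group = 2 (z₁₋α + z_power)² (SD/margin)². Power = Φ(margin / (SD √(2/n)) − z₁₋α).

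**1. Reproducing the appendix.** (21.6/5)² = 18.66. At one-sided 2.5% (z = 1.960):
- 90% power: 2 × (1.960 + 1.282)² × 18.66 gives 393.
- 95% power: 2 × (1.960 + 1.645)² × 18.66 gives 486.

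Both match exactly. The calculation was therefore done in kg, and 5 kg is not a slip for 5%. It also used one-sided 2.5%.

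**2. Same calculation at the SAP's level.** At one-sided 1.25% (z = 2.241), the sample sizes become 464 and 564. At 413 per group, SD √(2/n) = 21.6 × √(2/413) = 1.503, and 5/1.503 = 3.326:
- one-sided 2.5%: Φ(3.326 − 1.960) = 91.4%
- one-sided 1.25%: Φ(3.326 − 2.241) = 86.1%

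The five-point drop comes from the significance level, not from the unit of the margin.

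**3. Section 5.1.** 15 × √(2/1050) = 0.655. A 5 kg margin gives Φ(5/0.655 − 2.241), which is above 99.9%. Under the same assumptions, 90% power would need 224 per group, or would correspond at 1050 per group to a margin of (2.241 + 1.282) × 0.655 = 2.3 kg.

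**4. 5% against 5 kg.** The two are equal when 0.05 × W = 5, that is, W = 100 kg. Baseline weight is not given. At BMI 42 and an assumed height of 1.65–1.70 m it is 114–121 kg, so 5% is 5.7–6.1 kg. Over BMI 35–50 and heights of 1.60–1.80 m, 5% runs from 4.5 to 8.1 kg.

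Power at 413 per group on the percent reading:

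| Assumption | One-sided 2.5% | One-sided 1.25% |
|---|---|---|
| 5% of a mean baseline of 100–140 kg, SD 21.6 kg | 91.4–99.7% | 86.1–99.2% |
| 5 percentage points, SD of percent loss 8–18 points | 97.9% to >99.9% | 96.0% to >99.9% |

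The SD of percent weight loss is not in the documents; 8–18 points is an assumed range.

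**The case against.** The strongest reply is that the decision rule does not vary. Every rule-setting part of the SAP says 5%, and Table 1 points to percent of total body weight. The 5 kg appears once, in a calculation labelled post hoc, which does not claim to amend the margin. Percent change can be derived from the weight measurements in section 5.3. This largely stands: the intended scale can be inferred. But it has to be inferred, because no margin sentence gives the base and section 5.3 does not name the modelled response.

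A reader might also infer more than the documents support:

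- *That the trial is badly underpowered for weight.* Taking 5% of the mean loss gives 0.05 × 29.3 = 1.465 kg and about 10% power at 413 per group. Table 1 speaks against this reading, and the SAP nowhere names the mean loss as the base.
- *That inclusion was stopped on an inflated calculation.* If mean baseline weight is above 100 kg, 5 kg is the harder margin and the scale mismatch understates power. The decision also rested on adverse-event power and on not prolonging inclusion, and the DSMC supported it. Moreover, 413 per group reflects only the 1031 patients with 2-year data. The same 20% loss applied to 1752 leaves about 700 per group, and 98% power for 5 kg at one-sided 1.25%. That is optimistic, because loss before year 2 is not given.
- *That no reading yields the 90% in section 5.1.* This is unproven. With a 5 kg margin, a true SG deficit of about 2.7 kg gives 90%. Nothing suggests that was intended, but section 5.1 states neither its assumed true difference nor its attrition.

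The protocol also refers to a method article and to separate analysis plans for each publication, which may settle the unit but were not available here.

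**Conclusion.** The inconsistency is real and unexplained: a 5% margin on a percent-of-body-weight outcome, an SD in kg beside it in section 5.1, and a 5 kg margin in the appendix. What needs correcting is an incompletely defined threshold and power figures on the wrong scale. Inadequate power is not shown: on the percent reading, power at 413 per group is 86% or more for any mean baseline weight of 100–140 kg, and 96% or more if the SD of percent loss is 8–18 points. Those ranges are assumptions, though a mean above 100 kg is likely at BMI 35–50.

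Two stated figures need correction whatever the scale. The 90% in section 5.1 is not what a 5 kg margin gives under zero true difference and no attrition (above 99.9%). The appendix sample sizes use one-sided 2.5%; at the SAP's level they are 464 and 564, and power at 413 per group is 86% rather than 91%. The second is a separate error in the same calculation.

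**What to change.** Before the 5-year analysis, amend the SAP as follows:

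1. Define the margin once, in section 4, and refer to it elsewhere: SG is non-inferior if the 97.5% confidence interval for the 5-year difference in percent total body weight loss excludes a deficit of 5 percentage points or more.
2. In section 5.3, name percent weight change from baseline as the response in the primary mixed model, with the analysis in kg as supportive.
3. Restate the power in section 5.1 and the appendix on that scale, using the SD of percent weight loss from the 2-year data already held, the two-sided 2.5% level, and explicit assumptions on true difference and attrition.

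The cost is a few sentences and one recalculation. No new data are needed and no design decision is reopened.

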#### 5.4 Study follow-up and missing data

For evaluation of incidence of severe adverse events, it is expected that the coverage will be close to 100% as these are to be collected through national register linkage. Patients who withdraw consent will be censored right after withdrawal in time-to-event models. Patients who emigrate from Sweden or die before the end of 5-year follow-up will be censored at the time of emigration and date of death, respectively. All other patients not experiencing substantial adverse events during the study follow-up will be censored at the date of individual 5-year follow-up. The primary conclusions of the study will be based on analyses conducted on all randomized patients (with exception of those who withdraw their consent) under the principle of intention-to-treat.

For evaluation of non-inferiority, a sensitivity analysis will be conducted using both multiple imputation of missing body weight data, as well as last observation carried forward (LOCF) imputation. The results of these analyses will be reported together with results of the primary analysis.

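### The 87.5% post hoc power for substantial adverse events matches the planned analysis in neither sample size nor significance level; the net effect understates the power

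*Combined protocol and SAP*

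**What the plan says.** The SAP v5 Appendix reports two post hoc power calculations on data from February 2022.

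- **Item 1, weight.** It starts from "an average weight loss for all patients (both groups, N=1031") at two years and continues: "Given a loss to follow up of 20% from 2 year follow up to the 5-year follow up". Halving the result gives 413 per group.
- **Item 2, substantial adverse events.** "This post hoc power calculation is for a superiority test" in which "the rate is assumed to be 25% for the gastric bypass at 5 years" and "sleeve would have a 35% lower level", that is 16.25%. With 413 "per group the post hoc power will then be 87.5" per cent. Item 2 states no significance level and gives no separate reason for using 413.

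The rest of SAP v5 describes the analysis that this power should refer to.

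- **Section 5.2** tests each primary outcome at two-sided 2.5%, because there are two of them.
- **Section 5.3** analyses time to first substantial adverse event with a Cox model.
- **Section 5.4** bases the primary conclusions on all randomised patients except those who withdraw consent. Of adverse events it says "it is expected that the coverage will be close to 100% as these are to be collected through national register linkage".
- **The end of the Appendix** records: "At termination of inclusion the number of participants that had been included and operated in BEST were 1752".
- **Section 5.1** still gives a 13% event rate, 2100 patients and more than 90% power.

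**The concern.** A power figure should describe the test that will be run, on the patients who will be in it. Item 2 takes its sample size from the other primary outcome. That outcome needs a measured weight; the adverse-event outcome does not, because a patient without a 5-year visit is still followed through registers and otherwise censored. Using 413 leaves out 1752 − 1031 = 721 of the final participants and then applies a visit-loss rate to the remainder.

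The significance level also appears to differ from section 5.2, and this works the other way: a looser level raises the stated power. Correcting only one of the two inputs would produce another figure that does not describe the trial.

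Item 2 is the only adverse-event power figure given in support of closing inclusion at 1752 instead of 2100. It is also the figure against which a reader would judge a null result. In its present form it suggests that sample size is the limiting factor, when the assumed event rate matters far more.

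**Working it through.** **Inputs.** GBP risk p1 = 0.25 and SG risk p2 = 0.25 × 0.65 = 0.1625 (Appendix, item 2). Two-sided 2.5% (5.2), z = 2.2414; for comparison two-sided 5%, z = 1.9600. n = 413 (Appendix), or 1752/2 = 876 (end of Appendix, 1:1 allocation in 3.1).

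**Origin of 413.** 1031 × 0.80 / 2 = 412.4, given as 413.

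**Reproducing 87.5%.** Two proportions, pooled variance under the null:

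power = Φ{[(p1 − p2) − z·s0] / s1}, with p̄ = 0.20625, s0 = √[2p̄(1 − p̄)/n] and s1 = √{[p1(1 − p1) + p2(1 − p2)]/n}.

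At n = 413, s0 = 0.02816 and s1 = 0.02799.

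- z = 1.9600: Φ[(0.0875 − 0.05519)/0.02799] = Φ(1.154) = **87.6%**. This agrees with the plan.
- z = 2.2414: Φ[(0.0875 − 0.06312)/0.02799] = Φ(0.871) = **80.8%**.

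Other versions at two-sided 2.5% and n = 413 (unpooled 81.2%, continuity-corrected 78.4%, Fisher 78.7%, Schoenfeld with HR 0.616 82.0%) do not reach 87.5% either. A one-sided 2.5% test uses z = 1.9600 and gives the same 87.6%. The level behind item 2 is therefore inferred, since the item does not state it.

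**Planned analysis, full ascertainment (n = 876, two-sided 2.5%).**

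- Two proportions: s0 = 0.01933, s1 = 0.01922, Φ(2.298) = **98.9%**.
- Schoenfeld, power = Φ[(√d / 2)·|ln HR| − z]. If 35% is a reduction in risk, HR = ln(0.8375)/ln(0.75) = 0.616 and d = 876 × 0.4125 = 361 events: Φ(4.599 − 2.241) = **99.1%**.
- If 35% is a reduction in hazard, HR = 0.65, SG risk = 1 − 0.75^0.65 = 17.06% and d = 876 × 0.4206 = 368: Φ(4.134 − 2.241) = **97.1%**. Freedman's form, Φ[√d·(1 − HR)/(1 + HR) − z], gives **96.6%**.

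**With 20% lost (assumed; n = 1752 × 0.80/2 = 701).** Two proportions 96.5%; Schoenfeld with HR 0.616, 96.9%. With HR 0.65 (d = 295), Schoenfeld gives 92.7% and Freedman 91.9%. This treats lost patients as contributing nothing, which is stricter than censoring them.

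**At the 13% rate of section 5.1 (n = 876, two-sided 2.5%).** SG risk is 8.45%. Two proportions 79.9%; Schoenfeld with HR = ln(0.9155)/ln(0.87) = 0.634, d = 188, 81.1%. With HR 0.65 (SG risk 1 − 0.87^0.65 = 8.65%, d = 190), Schoenfeld gives 76.6% and Freedman 75.2%.

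| Setting, 35% reduction | Level (two-sided) | Power |
|---|---|---|
| 413 per group, 25%, two proportions | 5% | 87.6% |
| 413 per group, 25%, two proportions | 2.5% | 80.8% |
| 876 per group, 25% | 2.5% | 97–99% |
| 701 per group, 25% | 2.5% | 92–97% |
| 876 per group, 13% | 2.5% | 75–81% |

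**The case against.** The strongest reply is that the error is conservative and affects no test, margin or analysis set. The Appendix is a record labelled post hoc, recruitment closed in March 2022, and item 2 states openly that it is conditional on 413 per group. All of that stands, and it limits the point to a correction of the record.

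A second reply is that 1752 was not known in February 2022. That is fair for the exact figure. It does not explain a sample restricted to patients who already had a 2-year weight, because section 5.4 puts everyone randomised into this analysis.

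A third reply is that full ascertainment is optimistic. Several components in SAP Table 2 (food-related problems lasting at least three months, pain affecting daily life, reflux not controlled by medication) are not obviously visible in registers, and the protocol says complication data are collected at visits. This also stands. It is why 99% should not be quoted alone and why a 20% loss is shown. It does not justify a reduction to 413.

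Two stronger readings are tempting.

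- **A reader might infer that stopping early left this outcome underpowered.** Under the Appendix's 25% rate the recalculation shows the opposite.
- **A reader might take 413 as the expected number of 5-year weight completers per group.** It covers only patients with 2-year data in February 2022. Later 2-year visits are not counted, and the documents do not give the total to be expected.

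**Conclusion.** The point holds as a mismatch of inputs. The arithmetic of item 2 is sound for 413 per group at two-sided 5%, but neither the sample size nor the level is that of the planned analysis. The sample size understates power and the level overstates it. The first effect is larger, so on balance 87.5% is too low: about 97–99% under the plan's own 25% and 35% assumptions with full ascertainment, and about 92–97% with an assumed 20% loss. The decision to stop inclusion is not undermined for this outcome under the 25% assumption.

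The conclusion depends on the event rate. At 13% the same 876 per group gives about 75–81%, below the more than 90% that section 5.1 states for 2100 patients. That gap is not all due to stopping at 1752: at 13%, 1050 per group and two-sided 2.5%, the two-proportion formula gives 87.1% and Schoenfeld with HR 0.634 gives 88.1%.

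These figures take 1752 included and operated as a close stand-in for all randomised patients less consent withdrawals, equal groups, and proportional hazards.

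**What to change.** Restate item 2 of the Appendix as follows.

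- Use the intention-to-treat number (about 876 per group, replaced by the exact randomised count less consent withdrawals), two-sided 2.5%, and an event-based calculation matching the Cox model.
- Say whether the 35% is a reduction in risk or in hazard.
- Report power at the 25% rate (about 97–99% with full ascertainment; about 92–97% with 20% loss, marked as an assumption) and at the 13% rate of section 5.1 (about 75–81%).
- Label 413 as belonging only to the February 2022 weight calculation in item 1.

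The cost is one rewritten appendix paragraph. Design, conduct and analysis are unchanged.
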